### Strategies to enhance intervention adherence

2.8

To promote participant adherence to the intervention, the study will deploy the following measures:

Explicit Communication of Responsibilities: Responsibilities of participants over the duration of the period of observation would be clearly explained at the recruitment stage as well as at the time of informed consent. Attempt would be made to develop good rapport between participants and researchers such that there would be mutual commitment and trust.Comprehensive education and counseling: Throughout the study, participants will receive integrated education and counseling covering disease management, lifestyle modification, and the prevention of potential complications.Weekly System Use Observation: The research team shall extensively monitor participants from the intervention arm on a weekly basis on their use of the AI-HEALS system. It would keep participants continuously involved and serve to identify potential issues or poor points of participation early. Appropriate corrective action would be instituted as needed to continue ensure that there is involvement as well as adherence.

### Outcomes

2.9

#### Primary outcomes

2.9.1

The primary outcomes of this trial are changes in key physiological parameters among patients with mild-to-moderate stroke. These include: Blood pressure, Blood glucose, Blood lipid levels. Measurements will be collected at baseline, discharge, the end of the 3-month intervention, and at 3, 6, and 9 months post-intervention. These indicators constitute the primary endpoints as they represent the main clinical effects targeted by the AI-HEALS intervention.

#### Secondary outcomes

2.9.2

##### Self-management behaviors

2.9.2.1

Changes in self-management behaviors will be assessed across multiple domains, including: behavioral decision-making, nutrition preference, physical activity, medication adherence, smoking and alcohol control, sleep patterns, quality of life, functional autonomy in daily living.

##### Psychosocial and cognitive measures

2.9.2.2

These include: perceived recurrence/stroke risk, health literacy, self-efficacy, depression, anxiety, stress, perceived social support. These outcomes evaluate psychological and behavioral dimensions associated with secondary stroke prevention.

#### Exploratory outcomes

2.9.3

Exploratory outcomes reflect additional clinical, behavioral, and process-related indicators. These include Physiological monitoring indicators: level of consciousness, respiratory rate, heart rate and rhythm, height, weight, waist circumference, body mass index (BMI). Healthcare utilization indicators: 30-day hospital readmission and duration of hospital stay. Process indicators: recruitment and attrition rates, reasons for withdrawal, and differential characteristics between participants who discontinue the study and those who complete it.

### Variable measurement

2.10

Sociodemographic measures will be obtained at baseline. Physical examinations and questionnaire evaluation are scheduled at the following time points: baseline, at hospital discharge, at the end of the intervention, and at 3, 6, and 9 months post-intervention (Table 1).

**Table 1 tab1:** The schedule of enrolment, interventions, and assessments.

Study period	Recruitment	Intervention		Follow-up		
Timepoint	0	Discharge	3 Months	3 Months	6 Months	9 Months
Eligibility screen	✓					
Informed consent	✓					
Allocation	✓					
Sociodemographic variables	✓					
RRPS-SP	✓	✓	✓	✓	✓	✓
BDMS-SP	✓	✓	✓	✓	✓	✓
PHQ4	✓	✓	✓	✓	✓	✓
PSSS-SF	✓	✓	✓	✓	✓	✓
NGSES-SF	✓	✓	✓	✓	✓	✓
EQ-5D-5L	✓		✓	✓	✓	✓
Smoking	✓		✓	✓	✓	✓
Alcohol consumption	✓		✓	✓	✓	✓
B-PSQI	✓		✓	✓	✓	✓
FCS-SF	✓					
eHEALS	✓					

BDMS-SP, the Behavioral Decision-Making Scale for Stroke Patients; B-PSQI, The new Brief Version of the Pittsburgh Sleep Quality Index-Short Form; eHEALS, The eHealth Literacy Scale; FCS-SF, The Family Communication Scale-Short Form; EQ-5D-5L, EuroQol-5 Dimensions 5 Levels; PHQ-4, the abbreviated Patient Health Questionnaire-4; PSSS-SF, The Perceived Social Support Scale; NGSES-SF, The New General Self-Efficacy Scale-Short Form; RRPS-SP, Recurrence Risk Perception Scale for Patients with Stroke.

#### Sociodemographic variables

2.10.1

A specially prepared demographic questionnaire will be used to collect data on the following variables: sex, age, marital status, household registration, average number of persons per household, education, occupation, income, symptom of stroke, and detailed history of diseases.

#### Anthropometric variables

2.10.2

Height, weight, waist circumference, and blood pressure of each participant shall once be measured through certified equipment for accurate measurements. Height and weight shall once be obtained through duly calibrated and certified electronic weighing scales. BMI shall once be calculated as weight in kilograms divided by the square of the height in meters. Waist circumference once shall once be obtained at umbilical level through the use of a measuring tape. Blood pressure, including both systolic and diastolic measurements, will be obtained once using a validated automated sphygmomanometer (24). Venous blood samples were collected during hospitalization and at follow-up visits. Glycated hemoglobin (HbA1c) was measured to reflect the average blood glucose concentration over the preceding 2–3 months, providing an indicator of long-term glycemic control (25). Lipid profiles included total cholesterol (TC), triglycerides (TG), high-density lipoprotein cholesterol (HDL-C), and low-density lipoprotein cholesterol (LDL-C) (26). Serum TC and TG were measured using enzymatic methods, which employ specific enzyme reactions to convert target lipid components into detectable products, offering high sensitivity and specificity (26). Serum HDL-C and LDL-C were determined using homogeneous assays, in which specific chemical reactions uniformly disperse lipoproteins to enable quantification of cholesterol in each fraction (26).

#### Post-discharge engagement

2.10.3

Regular follow-up upon hospital discharge shall continue through WeChat communication, phone calls, or mobile texting. These contacts serve to keep participants continually informed and involved. Participants shall, at all times, receive prompt reports on the progress of the study, resolution of issues that arise, as well as scheduling of forthcoming follow-up assessments.

Standardized data entry of such research work shall be accomplished through an electronic data capture (EDC) system. A double entry system shall be utilized by two independent operators for validation, followed by logical checks of consistency of all raw data. The sensitive data shall be secured through encryption under the Unicode encoding scheme. The data shall be stored on password-protected servers, which implement role-based security that only allows authorized investigators to look at de-identified data. Additionally, a real-time backup system shall be put into action that transfers data to offsite cloud storage to ensure data integrity as well as facilitate disaster recovery.

Once participants’ data has been collected, all personally identifying information will be promptly removed to ensure confidentiality. This means that personal identifiers will be replaced by participant-specific codes. Only a limited number of authorized team members will obtain the linkage key that connects such codes to actual identities. The key will be kept separately at a highly secure site.

Under no circumstances will any personal data be disclosed to third parties without the participant’s explicit informed consent. Every member of the research team must also sign confidentiality agreements to commit them to utmost data privacy standards. From the time of study initiation to study completion, and even after study closure personal data of all types shall at all times remain safely stored on dedicated servers, which shall only be opened to authorized personnel only.

#### Questionnaire assessments

2.10.4

Recurrence Risk Perception Scale for Patients with Stroke, created by Lin Beilei et al. in 2021, will be used to assess patients’ perceived stroke recurrence risk (27). It is well suited for the population of interest of the current study. Although the original scale comprises two parts, only the second part will be used in this study. The first part, a visual analog scale, has neither established reliability nor validity and does not contribute to the total score. The second part consists of 17 items, spread over three dimensions: perceived risk of disease-related factors (4 items), perceived risk of behavioral factors (6 items), and perceived severity of recurrence (7 items). Each item has a 3-point Likert scale, from “Disagree” through “Agree,” which has a score of 1 to 3, respectively, with total scores of 17 to 51, respectively. The greater the score, the larger the perceived recurrence risk. The Cronbach’s *α* of the entire section is 0.850, of the three sections, 0.875, 0.815, and 0.804, respectively.

For the assessment of behavioral decision-making of patients suffering from mild stroke, the study will employ the Behavioral Decision-Making Scale for Stroke Patients, which has also been created by Lin Beilei et al. during 2022 (28). It has 30 items, spread over four dimensions: motivation for change of behavior (10 items), behavioral change intention (9 items), decision-making determinants (5 items), and decisional balance (6 items). It uses a 5-point Likert scale, on which the answers range from “Strongly Disagree” to “Strongly Agree,” on a 1–5 scale score. Its total score falls on a 30–150 scale, on which the larger values indicate larger behavioral decision-making capacity. Content validity of individual item falls on 0.800–1.000, while the total content validity falls on 0.975. Overall Cronbach’s α of the scale falls on 0.934, while the subscales record high internal consistency on 0.937, 0.933, 0.778, and 0.908, respectively.

Measurement of anxiety and depression will be conducted using the Patient Health Questionnaire-4 (PHQ-4), a brief self-report questionnaire designed to gage symptom presence over the past fortnight (29). The PHQ-4 includes four questions: the first two assess depressive symptom presence, and the final two assess anxiety symptom presence. Each question uses 4-point Likert scales, from “Not at all” (0 points) through to “Nearly every day” (3 points), such that the score range of the total lies between 0 to 12 points. The PHQ-4 has demonstrated notable validity and reliability on ethnically diverse populations, one validation study reporting 0.833 as Cronbach’s alpha of the Chinese version.

Perceived social support will be measured by the Perceived Social Support Scale–Short Form (PSSS-SF), which evaluates the perceived level of support of a person’s social network (30). Three items make up the scale, of which each one captures one of three specific types of support: family (item 1), friends (item 2), and other sources of support (item 3). Items are rated on a 7-point Likert scale from 1 (“Strongly disagree”) through 7 (“Strongly agree”) with a possible total score of 3 to 21. High values of the score indicate greater perceived available social support as well as the efficacy of the individual’s social network in supplying practical as well as affective support.

Participants’ self-efficacy as perceived ability to perform tasks or cope with demands will be assessed through the New General Self-Efficacy Scale–Short Form (NGSES-SF) (31). The three-item scale examines key self-efficacy facets: perceived ability (item 1), strength of confidence (item 2), and generality of confidence (item 3). Items use a 5-point Likert scale from 1 (“Strongly disagree”) through 5 (“Strongly agree”). Sum ratings of NGSES-SF total score range from 3 through 15. Higher ratings indicate greater self-confidence as well as a stronger perceived ability to cope with diversified demands.

The quality of life will be measured by the EuroQol-5 Dimensions 5 Levels (EQ-5D-5L) questionnaire. It is a well-validated instrument that measures five significant domains of health: mobility, self-care, usual activities, pain/discomfort, and anxiety/depression (32). Five response scales are provided for each of the five domains, from “no problems” to “extreme problems,” which allows respondents to select the best answer that reflects their current state of health at the moment of answering. These responses are used to obtain a complete health profile. In addition to the descriptive system, the EQ-5D-5L questionnaire includes a Visual Analog Scale (VAS), which permits respondents to self-rate the perceived current overall health on a 0-to-100 scale, from worst imaginable health to best imaginable health, providing a quantitative estimate of subjective well-being.

The smoking habit will be assessed by a specially prepared questionnaire consisting of four single-choice questions which attempt to capture participants’ smoking experience (33). The questions touch upon smoking history, years of abstinence (if ever smoked), cigarettes smoked daily, and initiation of smoking at what age. The first question has: “Do you currently smoke?” The options are: (1) Yes, traditional cigarettes; (2) Yes, electronic cigarettes; (3) Yes, both; (4) Used to smoke (stopped now); (5) Never smoked. Participants would be grouped into either current smokers or non-smokers (representing both never smokers and former smokers) based on these options.

Alcohol use assessment will also be conducted by a self-designed questionnaire consisting of seven single-choice questions seeking a total picture of participants’ consumption behavior (34, 35). The questionnaire includes whether the participant consumes alcohol, initiation and quit ages, alcoholic beverages consumed, consumption quantity per day, alcoholic beverages consumed before quitting, as well as quit-induced anxiety symptoms. Participants will respond to the question: “Do you currently or have you previously consumed alcohol?” as follows: (1) Never consumed alcohol; (2) Currently consumes alcohol; (3) Used to consume alcohol, but no longer does; (4) Did not consume alcohol previously, but currently does.

Sleep quality will be assessed through the use of the Pittsburgh Sleep Quality Index–Short Form (PSQI-SF), which is a shortened version of the initial PSQI, designed to evaluate the sleep quality of individuals (36). The PSQI-SF consists of six items from five core domains: sleep efficiency (items 1, 2), sleep latency (item 3), sleep duration (item 4), sleep disturbances (item 5), and subjective sleep quality (item 6). Wake time and bed time data, when available, are used for the calculation of sleep efficiency. The total score on the PSQI-SF ranges from 0 to 15, where elevated values reflect poor sleep quality and greater sleep issues.

The family communication will also be assessed by the Family Communication Scale–Short Form (FCS-SF), which identifies the quality of communication among family members (37). It consists of a four-item scale that captures one dimension of family communication, which is scored on a 5-point Likert scale from 1 (“Stronglydisagree”) through 5 (“Strongly agree”). The score varies from 4 to 20, of which greater values indicate more effective and healthier styles of communication among members of the family unit.

The Chinese version of the Electronic Health Literacy Scale (eHEALS) measures patients’ ability to search for, evaluate, and use electronic health information to solve health problems (38). The scale has five items on one dimension. It uses a 5-point Likert scale, where 1 indicates “strongly disagree” and 5 indicates “strongly agree.” The total score ranges from 5 to 25 points. Higher scores indicate better electronic health literacy.

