### Recruitment

2.5

This study shall enroll patients with mild to moderate stroke as outlined by the inclusion and exclusion criterion set, to evaluate the efficacy of the AI-HEALS intervention. Recruitment shall be done by the hospital clinical team, which shall screen potential participants upon admission and provide them with the option of enrolling into the study. Subsequently, the study team shall conduct face-to-face consultations, which shall involve clarifying the study goals, procedures, potential benefits, and associated risks. Eligible patients shall be asked to receive a thorough health evaluation, involving discussion of the history of their stroke and current symptom. Only when there shall be complete understanding of the study, including clarification of all questions, shall patients be asked to provide an informed consent form. The participants shall only enroll into the study upon signing of the written informed consent form. Over the three-month AI-HEALS intervention, assessments will be conducted at baseline (pre-intervention), at discharge, at the end of the intervention, and during follow-up. To encourage maximum patient participation, all participants will receive a free medical consultation at the end of the study as an incentive for their participation.

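### Smoking status is asked as of now during the stroke admission, and recent quitters are pooled with never smokers, so change and quit-rate analyses miscount patients who stop at the stroke

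*Protocol article*

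**What the plan says.** The Recruitment section (2.5) places enrolment in hospital: the clinical team is the one "which shall screen potential participants upon admission". Table 1 records smoking at baseline, at the end of the 3-month intervention, and 3, 6 and 9 months after that. It is not recorded at discharge.

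Section 2.10.4 (Questionnaire assessments) describes a self-designed four-item smoking questionnaire: "The first question has: “Do you currently smoke". No period before the stroke is given. The last two of its five answers are "4) Used to smoke (stopped now); (5) Never smoked". The grouping rule is then: "Participants would be grouped into either current smokers or non-smokers (representing both never smokers and former smokers) based on these options". The content of the questionnaire is summarised as: "The questions touch upon smoking history, years of abstinence (if ever smoked), cigarettes smoked daily, and initiation of smoking at what age".

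Section 2.9.2.1 lists "smoking and alcohol control" among the secondary self-management outcomes and frames that whole set as changes in behaviour. The Statistical analysis section (2.11) allows mixed models or simpler comparisons for secondary outcomes and does not name a smoking contrast.

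The alcohol item in 2.10.4 also has no reference period. One option is current drinking; another is "4) Did not consume alcohol previously, but currently does".

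**The concern.** The baseline answer is taken at a point when many smokers may have stopped because they are in hospital after a stroke. Someone who smoked up to the event can truthfully say that they have stopped. The stated rule then puts them with people who never smoked.

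This matters because the outcome is framed as change. Helping such a patient stay off cigarettes after discharge is one thing a post-discharge self-management tool might achieve, yet that patient is coded non-smoker at every visit. If they relapse, they look like someone who has taken up smoking. A quit rate calculated among baseline smokers leaves them out altogether.

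**Working it through.** The documents give no smoking prevalence, quit rate or smoking-based power, so there is no stated figure to reproduce. The check is algebra plus an illustration.

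**Inputs from the protocol:** 1:1 allocation (2.2); 30 per arm recruited (2.4); the question, the answers and the binary grouping (2.10.4).

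**Assumed inputs (not in the documents):**
- s = share who smoked before the stroke: 0.40, range 0.30 to 0.50.
- q = share of those who answer at baseline that they have stopped: 0, 0.5, 1.
- a1, a0 = share of pre-stroke smokers abstinent at follow-up: 0.60 with AI-HEALS, 0.40 with control, the same whatever the baseline answer.

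**Step 1: formulas under the stated grouping.**
- Current smoking at baseline: s(1 − q).
- Current smoking at follow-up: s(1 − a).
- Within-arm change: s(1 − a) − s(1 − q) = s(q − a).
- Between-arm difference at follow-up: −s(a1 − a0).
- Between-arm difference in changes, with q equal in the two arms in expectation by randomisation: also −s(a1 − a0).
- Sustained abstainers coded non-smoker throughout, per arm: 30·s·q·a.

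**Step 2: numbers for s = 0.40.** Follow-up smoking is 0.40 × 0.40 = 0.16 with AI-HEALS and 0.40 × 0.60 = 0.24 with control.

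| q | Coded smoker at baseline, per arm | Change, AI-HEALS | Change, control | Difference in changes | Abstainers coded as no change (AI-HEALS; control) |
|---|---|---|---|---|---|
| 0 | 12 | −0.24 | −0.16 | −0.08 | 0 of 7.2; 0 of 4.8 |
| 0.5 | 6 | −0.04 | +0.04 | −0.08 | 3.6 of 7.2; 2.4 of 4.8 |
| 1 | 0 | +0.16 | +0.24 | −0.08 | 7.2 of 7.2; 4.8 of 4.8 |

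The within-arm changes depend heavily on q and even reverse sign. The denominator of a quit rate falls from 12 to 6 to 0 per arm. The between-arm difference does not move. With s = 0.30 it stays at −0.06, and with s = 0.50 at −0.10.

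**Step 3: precision lost by including never smokers.** z = difference / SE, with SE = √[p1(1 − p1)/n + p0(1 − p0)/n].
- Pre-stroke smokers only, n = 0.40 × 30 = 12 per arm: difference 0.60 − 0.40 = 0.20; SE = √(0.24/12 + 0.24/12) = 0.20; z = 1.00.
- All 30 per arm: difference 0.24 − 0.16 = 0.08; SE = √(0.1344/30 + 0.1824/30) = 0.103; z = 0.78.
- For s = 0.30 (n = 9) the pair is 0.20/0.231 = 0.87 against 0.06/0.092 = 0.65. For s = 0.50 (n = 15) it is 0.20/0.179 = 1.12 against 0.10/0.111 = 0.90.

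The sharper contrast requires pre-stroke smokers to be identified, which a question about current smoking asked in hospital does not do reliably.

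**The case against.** A reader might infer that the smoking outcome cannot credit sustained quitting at all. The documents do not support that, for three reasons.

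- The comparison is randomised, and the expected between-arm difference in current smoking at follow-up does not depend on q. If AI-HEALS prevents relapse, fewer patients in that arm smoke at follow-up.
- A patient who reports smoking at baseline and later reports having stopped moves from smoker to non-smoker and is credited.
- Former and never smokers are separate answers when the data are captured. The pooled variable is derived and can be recoded.

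All three stand, and they limit the point to within-arm change, individual change and quit-rate analyses. The protocol does not commit to any of these, although it does frame the outcome as change.

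Recoding recovers only part of the loss. Separating former from never smokers does not separate a patient who stopped days ago from one who stopped long ago, and an abstinence item in years may be too coarse to do so.

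It can also be said that the article quotes only one of four questions, that the full questionnaire may set a reference period, and that a newly admitted smoker may simply answer yes. This is fair: the number affected is unknown. But the question, its answers and the grouping rule are all stated in the article, and as stated they allow the misclassification.

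On alcohol, the two overlapping options both mean current drinking and the article gives no alcohol grouping rule, so no outcome is shown to be affected.

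**Conclusion.** The point holds in a limited form. As worded, the baseline item and the grouping rule let patients who stop at the stroke be coded as non-smokers from the start. Change-from-baseline summaries then show their abstinence as no change and their relapse as new smoking, and a quit rate among baseline smokers omits them.

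The between-arm comparison of current smoking at follow-up remains unbiased. Its weakness is lost precision from never smokers: z of 0.78 rather than 1.00 in the illustration, or 0.65 rather than 0.87 and 0.90 rather than 1.12 at the ends of the assumed range. These figures rest on assumed smoking and abstinence rates and show direction and rough size only. Neither contrast is close to decisive with 30 per arm.

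The consequence for the trial is small: one secondary domain in a study that sizes itself as a pilot. It is worth correcting because the item is self-designed and the pilot is meant to inform a larger trial. The alcohol overlap is a wording fault and no more.

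**What to change.** - Ask smoking and drinking status at baseline for a stated period just before admission, for example the preceding 30 days.
- Keep former and never smokers apart in the analysis variable.
- Name the smoking contrast: abstinence at each follow-up visit among pre-admission smokers, or a comparison adjusted for pre-admission status, reported alongside current smoking in all participants.
- For participants already enrolled, ask pre-stroke status retrospectively at a visit that is already scheduled.
- Make the two overlapping alcohol options mutually exclusive.

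The cost is rewording two self-designed questionnaires and one grouping rule, with no added visits or participants. The drawbacks are some recall error, more so when pre-stroke status is asked retrospectively, and a small group of pre-admission smokers in a 60-person pilot. Abstinence in that group should therefore be reported as an estimate with its interval.
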